### Trial treatment withdrawal

Participants have the right to withdraw from the trial or trial treatment at any time, without giving a reason. Participants who withdraw from the trial or treatment will be given options in relation to future participation in the trial. They will be able to:

Withdraw from trial treatment only, but continue with all safety and efficacy assessments on the trial.Undergo a final safety close-out visit prior to full withdrawal, see online supplemental table 1.Withdraw from trial treatment and follow-up visits, no further tests will be performed and no further data or samples will be collected.

### Trial monitoring and oversight

FELL-HD is jointly sponsored by Cambridge University Hospitals NHS Foundation Trust and University of Cambridge. The Sponsor will assign a Clinical Trials Monitor who will monitor the trial team to ensure they are adhering to the protocol and regulatory requirements. The first monitoring visit will take place within 10 working days of the first participant commencing treatment. Monitoring will then take place regularly until the trial ends. Any changes to the monitoring plan will be updated in the monitoring plan agreement and risk assessment form associated with the FELL-HD trial.

There will be a Trial Management Group (TMG) consisting of the chief investigator, SI, trial coordinators, trial pharmacist, trial statistician and clinical trial monitor who will meet once a month to discuss the running of the trial.

There will also be a Trial Steering Committee (TSC), which is a multidisciplinary group comprising members who are jointly responsible for the overall supervision of the FELL-HD trial. This committee will include but is not limited to the members of the TMG, an independent chair, independent clinical or scientific experts, independent statisticians with relevant experience and representatives of people with lived experience of HD. The TSC will meet at least every 12 months while participants are receiving felodipine and at least once thereafter.

All trial documentation and any amendments will be reviewed by the sponsor and approved for submission to the relevant regulatory bodies. Once full approval has been received, the information will be communicated as appropriate with the trial team, TMG and TSC.

All personal data are stored on the University of Cambridge Secure Data Hosting Service, this is password protected and can only be accessed by the immediate trial team. All data entered into the electronic database are anonymised and entered under a specific participant trial ID for the wider trial team to access.

### Statistical methods

A statistical analysis plan (SAP) will be finalised and approved before the commencement of the analysis. The analysis will be performed on the modified intention-to-treat population, which includes all eligible participants who had at least one dose of investigational treatment and were not replaced during the trial. Participant data will be analysed according to their allocated cohort. The primary outcome is felodipine-related AEs, therefore, missing data are not expected. In all analyses, no imputation will be performed.

Participant data will be summarised by cohort. For the primary endpoint, no formal hypothesis testing will be performed. The statistical analysis will be mostly descriptive, with the number of felodipine-related AEs summarised by dosage for each cohort. All the exploratory endpoints described in the outcome measurement section will be summarised, and a significance test will be performed between baseline and week 57/62, using a paired t-test as the primary analysis and a Wilcoxon signed-rank test as the sensitivity analysis. No formal subgroup analysis will be performed. This trial has no predetermined ending criteria or formal interim analysis.

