## Methods and analysis

### Overview

FELL-HD is a phase II, open-label trial in people with early HD that aims to test the safety and tolerability of different doses of felodipine. The trial will investigate whether three different doses of felodipine are tolerated over a 58-week treatment period, followed by a 4-week washout follow-up period.

18 participants will be recruited and allocated to one of three cohorts in alternating fashion that will all receive felodipine. All participants will begin on 2.5 mg of felodipine with the dose being increased every 2 weeks from baseline to the cohort maximum dose, only if the previous dose has been tolerated. Cohort 1 will receive a maximum of 5 mg, cohort 2 will receive a maximum of 10 mg and cohort 3 will receive a maximum of 20 mg. The dosing schedule is summarised in table 1. Safety assessments will be performed every 2 weeks up to week 8 while participants reach their maximum allocated dose. Following this, clinical and safety assessments will be performed every 8 weeks until week 40. At week 48, a telephone visit will be performed and participants will then be seen at week 57 for safety and clinical assessments. A repeat telephone visit will be performed at week 58 which is when participants will end their treatment phase with felodipine. Clinical and safety assessments will then be performed at week 62 for the final trial visit. For the schedule of visits, refer to figure 1.

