### Outcome measures

The primary outcome measure for the FELL-HD trial is the number of adverse events (AEs) attributable to felodipine. An AE is any untoward medical occurrence in a participant that may or may not have a causal relationship to the treatment. Recording of AEs starts from the point of informed consent at the screening visit regardless of whether a participant has started the treatment or not.

Exploratory outcome measures of the trial include:

Changes in clinical measurements of HD using validated motor and cognitive assessment tools between baseline visit (week 0) and end of the trial (week 62).Change on a range of MRI volumetric measures between baseline (week 0) and end of the trial (week 62).

In the sample-study FELL-HD-s, the primary outcome measure is the change in mHTT levels in the blood between baseline (week 0) and end of the trial (week 62). The secondary outcome measurement is the change in neurofilament light chain (NFL) levels in the blood between baseline (week 0) and end of the trial (week 62).

Exploratory outcome measures of the FELL-HD-s-study include:

Change in level of felodipine in the blood between baseline and week 62.Change in level of felodipine in the CSF between baseline and week 57.Change in mHTT levels in the CSF between baseline and week 57.Change in NfL levels in the CSF between baseline and week 57.Change in level of glial fibrillar acidic protein (GFAP) in the blood between baseline and week 62.Change in level of GFAP in CSF between baseline and week 57.

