### Treatment allocation and dosing

Participants will be assigned to one of three dosing cohorts. Cohort 1 will receive a total of 5 mg daily, cohort 2 will receive a total of 10 mg daily and cohort 3 will receive a total of 20 mg daily. There will be six participants assigned to each cohort in an alternating fashion, that is, participant 1 will be allocated to cohort 1, participant 2 will be allocated to cohort 2, participant 3 will be allocated to cohort 3, participant 4 will be allocated to cohort 1 and so on. This will be performed by the trial coordinator.

All participants will start on 2.5 mg from baseline (week 0), if tolerated, all participants will have their dose increased to 5 mg at week 2 and cohort 1 will then remain on 5 mg until week 58. Those assigned to cohort 2 will have their dose, if tolerated, increased again to 10 mg at week 4 and will remain on 10 mg until week 58. Those assigned to cohort 3 will also have their dose increased to 10 mg at week 4 and then have their dose, if tolerated, increased for a third time to 20 mg at week 6 and will remain on 20 mg until week 58. Please refer to the dosing schedule in table 1.

The dose will only be increased where the previous dose has been tolerated, all judgements of intolerance will be at the PI discretion. Intolerance may be defined by an occurrence of an AE of moderate severity, which is either definitely or probably related to the felodipine. If a participant is unable to tolerate a dose, they will be moved back to the last dose they were able to tolerate within their cohort dosing. If the participant is already at the lowest dose then felodipine will be withdrawn. No dose rechallenge will be undertaken if a dose is reduced during the course of the trial.

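### The only stated analysis population can leave out dosed participants, and their recorded felodipine-related AEs, from the primary AE count

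*Protocol article*

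**What the plan says.** The Outcome measures section makes safety the primary question: "The primary outcome measure for the FELL-HD trial is the number of adverse events (AEs) attributable to felodipine". It also says that AE recording begins at consent, before any felodipine is taken.

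The Statistical methods section names a single population: "The analysis will be performed on the modified intention-to-treat population". Its members are defined in the same sentence; the set "includes all eligible participants who had at least one dose of investigational treatment and were not replaced during the trial". The section goes on to describe the primary endpoint without naming another set. It adds "The primary outcome is felodipine-related AEs, therefore, missing data are not expected", "In all analyses, no imputation will be performed" and "For the primary endpoint, no formal hypothesis testing will be performed". The primary result is therefore a descriptive tabulation of related AEs by dosage within cohort.

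On size, the Overview states "18 participants will be recruited and allocated to one of three cohorts in alternating fashion that will all receive felodipine", and Treatment allocation and dosing puts six in each cohort.

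Statistical methods is the only place in the article where replacement is mentioned. No passage says who may be replaced, for what reason, up to what time, or how often.

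**The concern.** Membership of the set depends on two things that can be settled after the first dose: whether the participant is replaced, and whether they are still regarded as eligible. For an outcome that counts harms of the drug, a population that depends on post-dose events is unsafe, because the harm itself may lead to the exclusion. The article shows at least one route by which a related AE can end treatment. Under Treatment allocation and dosing, intolerance may be defined by a moderate AE definitely or probably related to felodipine, and "If the participant is already at the lowest dose then felodipine will be withdrawn". Whether such a person would then be replaced is not stated.

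The excluded events would not be missing in the usual sense. They would have been collected and then left out by definition, so the statement that no missing data are expected gives no protection.

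The primary analysis has no hypothesis test, so the tabulated counts are the result. Cohorts of six mean that one person changes the picture. The Sample size calculation section says the data will be used to design a phase 3 trial.

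**Working it through.** **1. The plan's own figure.** 3 cohorts × 6 participants = 18, which agrees with the stated total. The article gives no alpha, power or effect size, so there is no power calculation to reproduce.

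**2. What the clause does.** The set requires three things: eligible, at least one dose, not replaced. Anyone never dosed already fails the second condition. The third can therefore change membership only by removing someone who was dosed. If replacement is in fact confined to undosed people, the clause has no effect and can be deleted without loss.

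**3. Effect of single replacements in one cohort.** Assume six retained participants, x of whom have a related AE, and r replaced participants who each had a related AE. The plan reports x/6; all dosed participants give (x + r)/(6 + r). The 95% intervals are Clopper-Pearson. The values of x and r are assumptions.

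| x | r | Stated set | All dosed | Difference |
|---|---|---|---|---|
| 0 | 1 | 0/6 = 0% (0 to 45.9%) | 1/7 = 14.3% (0.4 to 57.9%) | 14.3 points |
| 1 | 1 | 1/6 = 16.7% (0.4 to 64.1%) | 2/7 = 28.6% (3.7 to 71.0%) | 11.9 points |
| 2 | 1 | 2/6 = 33.3% (4.3 to 77.7%) | 3/7 = 42.9% (9.9 to 81.6%) | 9.5 points |

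These are proportions of participants with a related AE. The primary outcome is a number of AEs, and a replaced participant with several related AEs would take all of them out of the count.

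**4. Expected effect.** Let p be the probability that a dosed participant has a related AE, and s the share of those participants who are replaced. Suppose that only they are replaced, and that recruitment continues until six are retained. Then P(AE and retained) = p(1 − s) and P(retained) = 1 − ps, so the expected proportion in the stated set is p(1 − s)/(1 − ps). The expected number dosed per cohort is 6/(1 − ps). The article gives neither p nor s. Taking p = 0.30:

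| s | Expected proportion | Expected number dosed per cohort |
|---|---|---|
| 0 | 30% | 6.0 |
| 0.25 | 0.225/0.925 = 24.3% | 6.49 |
| 0.50 | 0.15/0.85 = 17.6% | 7.06 |
| 1 | 0/0.70 = 0% | 8.57 |

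At p = 0.20 the expected proportion is 15.8% for s = 0.25 and 11.1% for s = 0.50. The row s = 0 shows no bias, and s = 1 is an extreme that nothing in the article suggests.

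**The case against.** The strongest reply is that nothing in the article links replacement to AEs. That is correct. A reader might infer that the people excluded are chiefly those who could not tolerate felodipine, so that the set amounts to those who tolerated it. The documents do not support this. Under Treatment allocation and dosing, an intolerant participant first goes back to the last tolerated dose, and mandated withdrawal arises only at the lowest one. A participant who steps down stays in the trial and in the set, with the AE counted. Under Trial treatment withdrawal, a participant may also stop felodipine and continue all assessments, and unless replaced remains in the set.

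A reader might also infer that the bias is greatest in the cohort with most intolerance. That would require replacement to rise with intolerance across cohorts, which no passage shows. All cohorts start at the same dose, and the higher cohorts have more steps to fall back through before withdrawal. Nor can a contrast of withdrawals among all dosed with none among six retained stand in for the primary result, because retained participants can have related AEs and those are counted.

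The ineligibility limb is thinner. Eligibility is to be confirmed at screening, and no passage describes anyone being found ineligible after dosing. The exclusion follows from the wording, but how often it would apply is unknown.

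Finally, the full protocol or the statistical analysis plan may hold a replacement rule or a separate safety set. The absence of that detail from an article is not the fault raised here. The article does fix a population, with its exclusions, for the analysis that includes the primary endpoint. A safety set elsewhere would have to override that text, so the two would still need to be reconciled.

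**Conclusion.** The point holds in a conditional form. Followed as written, the stated population excludes any dosed participant who is replaced or later judged ineligible, together with any felodipine-related AEs already recorded for them. That is the wrong set for a primary outcome that counts such AEs.

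The size and direction cannot be fixed from the article. If replacement is unrelated to AEs, or never follows dosing, the AE proportion is not biased. If participants with related AEs are replaced, both the count and the proportion are too low: by about 10 to 14 percentage points in a cohort of six for one such person in the cases shown, or from 30% to an expected 24% or 18% under the assumed shares of a quarter and a half. Uneven replacement could distort the comparison of cohorts, but this is a possibility and has not been shown. The correction is still warranted, because safety is the trial's primary purpose and the change is very small.

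**What to change.** Define the population for the primary outcome and all safety summaries as every participant who took at least one dose of felodipine, regardless of replacement or later-found ineligibility. Keep the modified intention-to-treat set for the exploratory before-after outcomes. Report the number of participants replaced, with reasons, by cohort.

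The cost is a sentence or two in the protocol and the statistical analysis plan. No new data are needed for participants already dosed, since their AEs are recorded from consent. The downside is that the safety denominator may exceed 18, cohorts may be slightly unequal in size, and the AE counts may look slightly less favourable.

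### The primary safety result is a raw AE count with no time on drug beside it, and the reason given for expecting no missing data does not hold

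*Protocol article*

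**What the plan says.** Under Outcome measures: "The primary outcome measure for the FELL-HD trial is the number of adverse events (AEs) attributable to felodipine". Statistical methods describes a mostly descriptive analysis without a hypothesis test, "with the number of felodipine-related AEs summarised by dosage for each cohort". No measure of exposure is named with that count.

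On completeness, the same section says "The primary outcome is felodipine-related AEs, therefore, missing data are not expected" and then "In all analyses, no imputation will be performed".

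Trial treatment withdrawal lets participants leave at any time without a reason and offers three routes:

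- "Withdraw from trial treatment only, but continue with all safety and efficacy assessments on the trial"
- "Undergo a final safety close-out visit prior to full withdrawal"
- "Withdraw from trial treatment and follow-up visits, no further tests will be performed and no further data or samples will be collected"

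Treatment allocation and dosing adds that a participant who cannot tolerate a dose returns to the last tolerated one, or comes off felodipine if already at the lowest, with no rechallenge. Participants are analysed in their allocated cohort.

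**The concern.** There are two linked problems.

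**The stated reason.** The article moves from the kind of outcome (felodipine-related AEs) to an expectation of no missing data. Completeness depends on follow-up, and the third withdrawal route ends follow-up without a closing safety contact. The two sections do not fit together.

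**The raw count.** A number of events can be compared between groups only if the time in which events could occur is similar. Here, time on drug can shrink through withdrawal, and time at a given dose can shrink through dose reduction. Both responses are tied to tolerability, so the shortfall may depend on dose. A less well tolerated cohort could have less time on its assigned dose, and a count with nothing beside it would not show this.

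The aim is to learn whether three maximum doses are tolerated, and Sample size calculation says the data will inform a phase 3 design. A reader who ranks cohorts or doses by raw counts could be misled.

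**Working it through.** The article gives no power, rate or withdrawal figure for the primary outcome, so there is no stated result to reproduce. Withdrawal numbers and AE rates below are assumptions.

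**Inputs.** 6 participants per cohort and 3 cohorts (Treatment allocation and dosing); 58 weeks of treatment and 4 of follow-up (Overview); weekly doses (Table 1); terminal half-life of 25 hours (Introduction).

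**1. Exposure by design.** Planned time on drug per cohort is 6 × 58 = 348 person-weeks. Counting weeks in Table 1, with weeks 6–57 as 52 weeks:

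| Dose | Cohort 1 | Cohort 2 | Cohort 3 |
|---|---|---|---|
| 2.5 mg | 6 × 2 = 12 | 12 | 12 |
| 5 mg | 6 × 56 = 336 | 12 | 12 |
| 10 mg | – | 6 × 54 = 324 | 12 |
| 20 mg | – | – | 6 × 52 = 312 |
| Total | 348 | 348 | 348 |

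If the weekly AE rate in cohort 3 were the same at every dose, the raw count at 20 mg would be expected to be 312/12 = 26 times that at 10 mg, from duration alone.

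**2. Stopping early.** If m of 6 stop at week w, time on drug is (6 − m) × 58 + m × w.

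- 2 stop at week 8: 4 × 58 + 2 × 8 = 248; 248/348 = 0.713, a loss of 28.7%.
- 1 stops at week 8: 5 × 58 + 8 = 298; 298/348 = 0.856, a loss of 14.4%.
- 1 stops at week 40: 5 × 58 + 40 = 330; 330/348 = 0.948, a loss of 5.2%.

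At an assumed constant rate of 1 related AE per participant over 58 weeks, the expected count of 6 falls to 248/58 = 4.3 in the first case, while the rate per person-week is unchanged. The figure is the same if the two stop treatment and attend every remaining visit, since it measures time on drug and not missing records.

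**3. Dose reduction.** Suppose 2 of 6 in cohort 3 move from 20 to 10 mg at week 8. Time at 20 mg becomes 4 × 52 + 2 × 2 = 212 of 312 person-weeks (68%), and time at 10 mg becomes 12 + 2 × 50 = 112. Total time on drug is still 348, so only a split by dose level shows the change.

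**4. How much could be hidden.** A cohort with 1.5 times the AE rate would match a fully treated cohort's raw count if m participants stopped at week 8, where m = 6 × (1 − 1/1.5)/(1 − 8/58) = 2/0.862 = 2.3.

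**5. AEs actually missing.** The chance of at least one full withdrawal among 18 is 1 − (1 − p)^18. It is 0.31 for p = 2%, 0.60 for 5%, 0.85 for 10% and 0.98 for 20%. Some incomplete follow-up is therefore likely unless full withdrawal is rare. However, five half-lives are 5 × 25 = 125 hours, or 5.2 days, so the period after exit in which attributable AEs are likely to arise is short.

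**The case against.** The case against has real force.

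- **Few attributable AEs should follow exit.** The outcome is AEs attributable to felodipine, and a full leaver is off the drug. Most later weeks are near to true zeros. This stands. A reader might infer that the plan silently imputes the most favourable value for all the unobserved weeks. The documents do not support that: nothing says such weeks count as none, and participants who are replaced are left out of the analysis set altogether.
- **The wording is milder than it may appear.** The article says missing data are not expected. It does not claim they are impossible, and two of the three withdrawal routes keep some safety information. This stands too.
- **AEs that lead someone to leave come before leaving.** They can be recorded, with safety assessments every 2 weeks up to week 8. This stands, and it means a downward bias in the least tolerated cohort is possible but not shown. The 1.5-fold example needs more than 2 of 6 to stop early merely to level the counts.
- **The analysis plan may add exposure tables.** That is a fair caution, since the article is condensed. But the article itself fixes the primary summary as a number by dosage and cohort, and the faulty inference stands whatever the analysis plan adds.

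The phrase about dosage can also be read as the cohort's assigned dose. On that reading the 26-fold contrast does not arise, but withdrawal and dose reduction still make exposure unequal.

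**Conclusion.** The point holds in a limited form. The inference from outcome type to complete data is unsound and conflicts with the withdrawal option under which "no further tests will be performed and no further data or samples will be collected". The direct loss of attributable AEs is probably confined to those unreported at exit or arising within days. The more important defect is a primary summary of raw counts over time on drug that is unequal by design across dose levels and may become unequal between cohorts.

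The 29% rests on two assumed stops at week 8 and a constant weekly rate. If AEs cluster early, the loss of events is smaller; if they build up later, it is larger. The figure sizes lost exposure and should not be read as a share of AEs gone missing. Nor do the documents show that the trial would give a false impression of safety; they show only that the stated summary could not reveal one.

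The change should be made, but the issue is not fatal: the analysis is descriptive and no test depends on it.

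**What to change.** 1. Delete the sentence that derives an expectation of no missing data from the type of outcome. State instead that AE observation ends at full withdrawal and may be incomplete around that time.
2. Keep the raw count and report beside it, by cohort and dose level, person-weeks on drug, related AEs per person-week, and the number of participants with at least one related AE.
3. Tabulate withdrawals by cohort, separating treatment-only from full withdrawal, with timing and any reason given.
4. Do not count an unexplained withdrawal as a felodipine-related AE. It has no causality assessment, and the article rules out imputation. Show it as a separate tolerability line.

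The cost is a wording change and one table, provided dates of dose changes and withdrawal are captured; the article does not say whether withdrawal dates are. Rates per person-week assume a roughly constant hazard and will be unstable in the 12 person-week escalation cells, which is why the raw counts should stay alongside.

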### Sample size calculation

As this is the first trial to investigate felodipine in patients with HD, there are insufficient data to conduct a formal assessment of the anticipated effect size. The preliminary data from this trial will provide the necessary information to design a further phase 3 trial that is sufficiently powered to show this.

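### Counting related AEs by dosage within each cohort mainly reflects time on each dose, and rates by dosage would not repair it; the main dose summary should compare allocated cohorts over the same weeks

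*Protocol article*

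**What the plan says.** The primary outcome is the number of AEs attributable to felodipine (Outcome measures). Statistical methods gives its tabulation, "with the number of felodipine-related AEs summarised by dosage for each cohort", and adds: "For the primary endpoint, no formal hypothesis testing will be performed". The same section states the basis of analysis: "Participant data will be analysed according to their allocated cohort".

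On allocation: "There will be six participants assigned to each cohort in an alternating fashion". Everyone starts at 2.5 mg, with steps at weeks 2, 4 and 6 up to the cohort maximum of 5, 10 or 20 mg (Table 1). Each step is conditional: "The dose will only be increased where the previous dose has been tolerated". According to Treatment allocation and dosing, intolerance may be defined by a moderate AE that is probably or definitely related to felodipine. A participant who does not tolerate a dose moves back to the last tolerated one, or comes off felodipine if already at the lowest. A reduced dose is not tried again.

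No AE rate is assumed anywhere. Sample size calculation says that "there are insufficient data to conduct a formal assessment of the anticipated effect size".

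**The concern.** Each cohort passes through two to four dosages, so a split by dosage within cohort naturally places those dosages side by side. Three features of the design prevent such a row from showing tolerability by dose.

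- **Exposure.** Titration doses are scheduled for 2 weeks each and the cohort maximum for 52 to 56 weeks. A count is mostly a measure of time.
- **Time since first dose.** On schedule, 2.5 mg is taken only in weeks 0-1 and 20 mg only from week 6. Any AE tied to starting the drug is credited to the lowest dose.
- **Selection by the outcome.** A related AE can itself decide whether someone reaches or keeps the next dose. AE-prone people build up time at low doses and are under-represented at high ones.

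The first feature inflates the top dose in counts. The other two deflate it in rates. A reader of this dose-finding trial could draw opposite conclusions from the same events, and the article does not say how the split is to be read.

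**Working it through.** **1. The plan's own figures.** 3 cohorts x 6 = 18 participants. Scheduled person-weeks per six participants, from Table 1 with all doses tolerated:

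| Cohort | 2.5 mg | 5 mg | 10 mg | 20 mg | Total |
|---|---|---|---|---|---|
| 1 | 12 | 336 | - | - | 348 |
| 2 | 12 | 12 | 324 | - | 348 |
| 3 | 12 | 12 | 12 | 312 | 348 |

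The total is 6 x 58 = 348 in each cohort.

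**2. Counts with no dose effect.** With a constant rate r and every dose tolerated, the expected count is r x person-weeks. In cohort 3 the ratio of 20 mg to 2.5 mg is 312/12 = 26. At an assumed r = 0.05 per week the counts are 0.6, 0.6, 0.6 and 15.6.

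**3. Adding start-up AEs.** Multiply the rate in weeks 0-1 by four (assumed). Counts become 2.4, 0.6, 0.6 and 15.6, and rates become 0.20, 0.05, 0.05 and 0.05. Counts single out 20 mg and rates single out 2.5 mg, although dose has no effect.

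**4. Adding selection.** This was simulated with the article's schedule, step-back and no-rechallenge rules. Assumed inputs:

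- weekly related-AE rate = 0.05 x (dose/2.5)^b x a personal gamma factor with mean 1 and variance 1;
- b = 0.5 (true 20 v 2.5 mg ratio = 8^0.5 = 2.83) or b = 0 (no dose effect);
- half of related AEs cause a permanent step down.

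The milder case uses 0.03 per week and 30% stepping down. Cohort 3 results at 2.5 / 5 / 10 / 20 mg:

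| Assumed truth | Count per six people | Weekly rate | Rate ratio 20 v 2.5 mg (true) |
|---|---|---|---|
| No dose effect | 2.1 / 2.5 / 3.4 / 5.6 | 0.071 / 0.066 / 0.053 / 0.031 | 0.43 (1) |
| Dose effect | 3.2 / 4.6 / 6.1 / 7.7 | 0.070 / 0.078 / 0.080 / 0.064 | 0.91 (2.83) |
| Dose effect, milder | 1.3 / 2.6 / 5.4 / 10.3 | not tabulated | 1.11 (2.83) |

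**5. A second model.** Base rate 0.03 per week, log-normal personal factor (SD of the log), and an early excess 1 + h x exp(-week/3). Cohort 3 weekly rates at 2.5 / 5 / 10 / 20 mg, with b = 0.5 unless stated:

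| Case | Rates | Order shown |
|---|---|---|
| Neither bias | 0.030 / 0.043 / 0.059 / 0.085 | true order |
| Early excess only, h = 2 | 0.082 / 0.080 / 0.086 / 0.086 | hidden |
| Early excess only, h = 5 | 0.158 / 0.137 / 0.128 / 0.089 | reversed |
| Selection only, SD 1, 30% stepping down | 0.051 / 0.063 / 0.064 / 0.053 | hidden |
| Both (h = 5) | 0.089 / 0.077 / 0.064 / 0.051 | reversed |
| Both, no dose effect | 0.103 / 0.067 / 0.041 / 0.021 | false protective trend |

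Either mechanism alone is enough to hide a dose effect.

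**6. Allocated cohorts, weeks 6-57.** These are 52 of 58 treatment weeks (90%). The denominator is all 52 weeks of every dosed person, on drug or not.

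- First model, dose effect: 0.034 / 0.047 / 0.062 for cohorts 1 / 2 / 3, a 20 v 5 mg ratio of about 1.8 against a true 4^0.5 = 2.0.
- First model, no dose effect: ratio about 1.28.
- Start-up AEs only: ratio 1.00.
- Second model, both biases: 0.026 / 0.036 / 0.047 with the dose effect. With no dose effect, 0.0229/0.0211 = 1.09.

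In weeks 4-5 the first model with a dose effect expects only about 0.7 events in cohort 1 and 2.0 in cohorts 2 and 3 together.

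**The case against.** The strongest reply is that this is a descriptive listing in a plan that already analyses by allocated cohort, with no test attached, and that table layout belongs in the SAP. Much of that stands. The allocated-cohort summary covers weeks 6-57 for 90% of its scheduled time, so most of the remedy is already present. What remains is that the article names the by-dosage split for the primary outcome and attaches no caution. If the dosage meant there is simply each cohort's assigned dose, the problem largely disappears, but the sentence should then say so.

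A reader might infer more than the text supports:

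- *That the stated table makes high doses look safe.* The article plans numbers, not rates. In every simulated case above, the count is highest at 20 mg. The opposite lean arises only if the counts are turned into rates.
- *That between-cohort comparison is missing.* The allocated-cohort sentence in Statistical methods contradicts this.
- *That doses always rise and are wholly confounded with time.* First exposure does follow a rising order, but the step-back rule puts some people on low doses late. This strengthens the selection.
- *That the cohort contrast is clean.* It is not. Step-down dilutes it. Withdrawal from drug is likelier in the 5 mg cohort, which has fewer steps to fall, hence about 1.28 with no dose effect. Allocation alternates and n = 6.

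The assumed inputs are also severe in the main case: about 21% of cohort 3 are still on 20 mg at the end and about 40% of cohort 1 are off drug. The milder case still shows 1.11 against 2.83.

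**Conclusion.** The point holds, at moderate severity. That counts by dosage follow exposure comes directly from Table 1 and needs no assumption beyond the schedule being followed. That rates by dosage can hide or reverse a dose effect follows from the titration order and the tolerance rule. Its size does not: 0.91 or 1.11 against a true 2.83, and 0.43 against a true 1, rest on assumed AE rates, variation between people and step-down probabilities. If there were no start-up excess and no selection, rates by dosage would recover the true order.

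The allocated-cohort comparison is less biased in these scenarios (about 1.8 against 2.0; 1.00 to about 1.28 against 1), but imprecise. The harm is to interpretation. No error rate is affected, so this is not a defect that must be cured before the trial can proceed.

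**What to change.** Before analysis, state in Statistical methods or the SAP:

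1. The main dose summary of related AEs compares allocated cohorts over weeks 6-57. It gives events, participants with at least one event, and person-time, with every dosed member of the modified intention-to-treat population in the denominator, including those who never reached the cohort dose.
2. Weeks 0-3, when all cohorts share one schedule, are pooled as a start-up period. Weeks 4-5 are shown descriptively.
3. For each cohort, report how many reached, stepped down from or stopped the cohort dose.
4. The by-dosage listing is kept, with time on each dose and a sentence that dosages are not to be compared within a cohort.

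The cost is one re-specified table and a short text change, with no new data. Weeks 0-3 give no dose contrast, and the limits of the cohort contrast (six per cohort, alternating allocation, dilution by step-down, unequal withdrawal from drug) should be stated beside the table.
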